### Procedure for unblinding if needed {17b}

If unmasking of the research technologist is deemed necessary, the clinical center investigator will notify the Data Coordinating Center and note the reason for unmasking on the data collection form. Investigators will be encouraged to maintain masking unless there is reason to believe that unmasking the research technologist is deemed to be in the best interest of the participant’s safety.

## Data collection and management

### Plans for assessment and collection of outcomes {18a}

Plans for assessment and collection of outcomes are discussed in the “Outcomes {12}” section.

#### Training and certification of study personnel

All study personnel responsible for recruiting, enrolling, collecting, and entering INVENT VPT data will receive role-specific training on the study procedures to include virtual and in-person training sessions, written examinations, and direct observation sessions. Study procedures, including the follow-up schedule, data collection, completion of the data collection forms, and the data entry and data quality query protocol will be discussed during live and recorded presentations. Personnel who satisfactorily complete all INVENT VPT training and receive passing scores on written examinations/direct observation sessions will be certified to participate in the INVENT VPT and will receive a certification ID to be used as a personnel identifier on all study documents.

### Plans to promote participant retention and complete follow-up {18b}

Study coordinators will develop a schedule for contacting participants by email, telephone, or text message (depending on the participant’s preference for contact) to remind them of upcoming study visits and to remind them to continue their study-assigned rehabilitation and other related procedures while at home.

We will also share the results of testing, including the video head impulse test reflecting the integrity of the vestibulo-ocular reflex measures, with participants at the conclusion of INVENT VPT Trial participation and include comparisons with age-matched controls.

### Data management {19}

Clinical center personnel who have been certified for INVENT VPT data entry will be provided access to the REDCap data system that will be used for data entry and access to the data for their center only. We have designed a double data entry system with an automated range and missing data checks upon entry. Inconsistencies will be further checked after entry via a series of programs that are designed to detect specific within-form and cross-form errors. Data quality query reports will be distributed biweekly to each clinical center for resolution. The study coordinator will be responsible for making corrections to the data system based on the queries that are distributed. The REDCap data system records all entries to maintain an audit trial of changes to the data system. Each clinical center will be responsible for responding to all queries and returning their responses to the Data Coordinating Center (DCC) for review.

### Confidentiality {27}

Participants who agree to be screened for eligibility will be assigned a study ID that will be used on all data collection forms. All data will be associated with the anonymous number and personal information will no longer be used. All data are stored on secured password-protected media. There will be a master document that links identifiable information with the anonymous identifier. This master document will only be accessible to the study coordinator. All participant study documents will be stored in a locked cabinet in a location with controlled access.

### Plans for collection, laboratory evaluation, and storage of biological specimens for genetic or molecular analysis in this trial/future use {33}

Biological specimens are not collected in this trial.

## Statistical methods

### Statistical methods for primary and secondary outcomes {20a}

The primary outcome for determining treatment efficacy is VOR gain, which is measured weekly for each subject in each intervention period. To verify randomization between sequences, baseline demographics and characteristics of vestibular injury will be compared across arms. The primary analysis will follow the intent to treat principle, where patient outcomes are analyzed following how they were randomized and not adjusted or excluded based on adherence to assigned treatment. To determine the efficacy for the primary outcome, a generalized linear mixed model will be used with VOR gain as the dependent factor [31]. This model will be used to compare VOR gain between interventions and to estimate period and carryover effects. With substantial washout periods for each aim, we do not expect there to be substantial differences in the carryover effects between intervention sequences. We will verify there are no differences in the carryover effects by testing for an interaction between treatment and time. If this interaction is statistically significant at *α =* 0.05, we will focus our analysis on patient outcomes in the first period, and disregard outcomes in the following period. We will adjust this model for site as well as demographic and vestibular injury-related factors that are imbalanced between arms at baseline. All statistical tests will be conducted as two-sided for an *α* of 0.05.

For secondary analyses, we will examine the compensatory saccade metrics, which are also measured at each weekly visit similarly to VOR gain. Similar to our analysis of the primary outcome, we will examine this secondary outcome with a generalized linear mixed model, estimating carryover effects by testing for an interaction between period and intervention. We will also adjust these comparisons of VOR gain and compensatory saccade metrics for site and for factors that are imbalanced at baseline. Analyses with greater than 25% loss to follow-up or incompleteness for other reasons will use multiple imputation [31]. All analyses will be conducted using the SAS software version 9.4 (SAS Institute Inc., Cary, NC, USA).

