### Trial design {8}

INVENT VPT is a randomized controlled crossover trial in which participants are allocated in a 1:1 ratio to initially receive the current standard of care vestibular rehabilitation method based on recent clinical practice guidelines (VPT) or incremental vestibular adaptation training (IVE). The novel incremental velocity error (IVE) method of vestibular training uses a device developed from laboratory studies to increase/normalize the gain/response of the vestibulo-ocular reflex (VOR).

Aims I–III include a crossover design with a washout period—though the duration of the aims and washout periods vary. After the washout period, participants will then receive IVE (if randomized to initially receive VPT) or VPT (if randomized to initially receive IVE). The outcome measures recorded after the washout on the 1st return visit are incorporated into the respective training for both arms. For example, participants are given balance exercises depending on their functional ability, which may change if the arm provides such an effect thereby minimizing any carryover effect during washout. Each participant recruited for the INVENT VPT Trial will receive a home exercise program to complete and be seen weekly in the clinic for exercise progression. The home exercises consist of gaze stability training (IVE or VPT) and gait/balance exercises. Exercises (gaze stability and gait/balance exercises) within the VPT intervention are developed based on the clinical practice guidelines [17]. Participants receiving IVE will use the IVE device and perform the same gait/balance exercises as participants receiving VPT. Each aim will include newly recruited participants so participants from one aim will not be eligible to participate in subsequent aims. Aim IV is an exploratory aim using data from all three prior aims. There is no additional data collection for aim IV.

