#### Intervention description {11a}

For aim I, we will randomize participants to the control (VPT) or experimental (IVE) group. For the following 6 weeks, participants in each group will be seen weekly for the progression of their gaze and gait stability exercises. Gaze stability will be for a total of 15 min per day for each group. After 6 weeks, participants will enter the washout stage for 6 weeks and not perform any explicit rehabilitation. Following the washout, participants will cross over into the other treatment group and complete another 6 weeks of IVE or VPT rehabilitation (Fig. 2).

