**Fig. 3 Fig3:**
[figure not shown]
Algorithm of aim II examining how training gaze stability alone impacts improvement considering 3-week washout and crossover design. Gait/balance exercises do not start until after the washout

For aim III, we seek to identify a minimum effective dose of gaze stability training. To do this, IVE and VPT participants will each complete their respective gaze stability training every other day. Both groups will complete the same gait/balance exercises from the start of the aim. Excluding the duration, the flow of aim III (Fig. 3) is similar to aim I.

For all aims, the intensity of the exercise program will be determined at the baseline visit based on the validated findings of the Dizziness Handicap Inventory, gait speed, and functional gait assessment (Table 1). Scores on each of these assessments will be summed for a composite impairment score. The composite score will inform the development of the exercise program to address the severity of impairment.

**Table 1 Tab1:** Schedule of enrollment and assessments in the INVENT VPT Trial

Study period				
Enrollment/baseline and randomization	Interventions	Follow-up assessments		
		vHIT	Participative measures	Impairment measures
**Eligibility screen** **Informed consent** One-time VOR characterization • Videonystagmography • Ocular and cervical vestibular evoked myogenic potential • Rotary chair • Video head impulse test • Audiogram • Clinical vestibular exam • Static visual acuity • Seated blood pressure **Randomization** • Treatment intensity ♦ Dizziness Handicap Inventory ♦ Gait speed ♦ Functional gait assessment	**Aim I** IVE-VPT VPT-IVE 6-week washout	Weeks 1–6 Weeks 13–18 6 months	Weeks 1, 4, 6 Weeks 13, 16, 18 6 months	Weeks 1, 4, 6 Weeks 13, 16, 18 6 months
	**Aim II** IVE-VPT VPT-IVE 3-week washout	Weeks 1–3 Weeks 7–9 6 months	Weeks 1, 3 Weeks 7, 9 6 months	Weeks 1, 3 Weeks 7, 9 6 months
	**Aim III** IVE-VPT VPT-IVE 3-week washout	Weeks 1–3 Weeks 7–9 6 months	Weeks 1, 3 Weeks 7, 9 6 months	Weeks 1, 3 Weeks 7, 9 6 months

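### The primary model names neither a primary time point nor a role for each period's first VOR gain measurement, so pre-training values can count as outcomes and dilute the IVE-VPT estimate

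*Protocol article*

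**What the plan says.** Statistical methods {20a} defines the primary outcome as "VOR gain, which is measured weekly for each subject in each intervention period". On the contrast it says: "This model will be used to compare VOR gain between interventions and to estimate period and carryover effects". On covariates it says: "We will adjust this model for site as well as demographic and vestibular injury-related factors that are imbalanced between arms at baseline". The only time term it mentions is the carryover check, made by "testing for an interaction between treatment and time". No visit is named as primary, and VOR gain before each period's training is not named as a covariate.

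Table 1 schedules the vHIT at "Weeks 1–6 Weeks 13–18 6 months" in aim I and at "Weeks 1–3 Weeks 7–9 6 months" in aims II and III. It also lists a vHIT in the one-time characterization at enrollment.

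Trial design {8} describes the visit that opens the second period: "The outcome measures recorded after the washout on the 1st return visit are incorporated into the respective training for both arms". For aim I, Intervention description {11a} gives the timing: "After 6 weeks, participants will enter the washout stage for 6 weeks".

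**The concern.** A measurement used to set up the coming training cannot show the effect of that training. If it enters the model as an outcome under the new intervention, it contributes a difference of zero, apart from any carryover, and pulls the estimate towards zero. With three visits per period, as in aims II and III, it is a third of the data.

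The missing time point adds to this. If VOR gain changes gradually, a treatment effect averaged over all weeks is smaller than the effect reached by the end of training. Sample size {14} is built on a change from before to after adaptation. The analysis as described neither uses the before value as a baseline nor singles out the after value. At stake are an understated effect, unused precision from period baselines, and freedom to choose the time point after seeing the data. The dilution does not create false positive results.

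**Working it through.** **1. The plan's own figure.** Inputs from Sample size {14}: change 0.19, SD 0.18, power 0.8, α 0.05 (two-sided per Statistical methods {20a}). The normal approximation gives n = (1.960 + 0.842)² × (0.18/0.19)² = 7.04, so 8. The exact paired t-test gives power 79.2% at n = 9 and 84.3% at n = 10. The stated 9 reproduces within rounding, and 9/(1 − 0.25) = 12 also reproduces. This is a one-group change in healthy adults and not an IVE-VPT difference, so it serves below only as a scale.

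**2. Is the first visit of period 2 before training?** Aim I: 6 weeks of training plus 6 of washout is 12, so week 13 opens period 2. Aims II and III: 3 + 3 = 6, so week 7 opens period 2. Trial design {8} says the measures from that visit feed into the training. The value is therefore in effect a period baseline.

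**3. Cost of the first visit alone.** With equal weights and V visits per period, a first visit with zero effect multiplies the average over the later visits by (V − 1)/V. This is 5/6 for V = 6 and 2/3 for V = 3, a loss of 1/6 or 1/3. It assumes that both periods start with a pre-training value. If only period 2 does, and week 1 already shows the later effect, the loss averaged over the two periods is (0 + 1/6)/2 = 1/12 or (0 + 1/3)/2 = 1/6.

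**4. Adding the build-up.** The documents give no time course, so the profiles are assumptions. Entries are shares of the end-of-training effect.

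| Assumed profile | All visits, aim I | All visits, aims II/III | Without visit 1, aim I | Without visit 1, aims II/III |
|---|---|---|---|---|
| Linear from 0 | 0.50 | 0.50 | 0.60 | 0.75 |
| Fast exponential | 0.74 | 0.58 | 0.89 | 0.87 |
| Complete by visit 2 | 0.83 | 0.67 | 1.00 | 1.00 |
| Late (quadratic) | 0.37 | 0.42 | 0.44 | 0.63 |
| Linear, visit 1 after one week of training | 0.58 | 0.67 | 0.67 | 0.83 |

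Example for the linear row, aim I: (0 + 0.2 + 0.4 + 0.6 + 0.8 + 1)/6 = 0.50; without the first visit, 3.0/5 = 0.60.

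**5. Check in a simulated crossover mixed model.** 24 participants, 60 runs, linear build-up to 0.19. The treatment coefficient over all visits was 0.095 for both schedules. As change from the first visit, averaged over later visits, it was 0.112 (6 visits) or 0.140 (3 visits). At the last visit, from a treatment-by-visit model, it was 0.188 or 0.186.

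**6. What this means on the plan's scale.** With SD held at 0.18, an effect of 0.095 in place of 0.19 needs 31 participants by the exact t-test, against 10, and power at n = 9 falls from 79% to 29%. With the first visit removed under linear build-up the requirement is 22 (aim I) or 15 (aims II and III).

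**7. Power of alternative contrasts.** 36 participants per aim (48 less 25%), end-of-training difference 0.10. The assumed SDs are 0.14 participant, 0.08 participant-by-period and 0.08 residual, which combine to 0.18. Results are for 6 / 3 visits:
- Linear build-up: all-visit average 66% / 61%; last visit 96% / 95%; last visit adjusted for the first-visit difference 99% / 98%.
- Complete by visit 2: all-visit average 98% / 86%; last visit 95% / 95%.
- Linear, participant-by-period SD 0.04 and residual SD 0.12: all-visit average 90% / 74%; last visit 89% / 91%.
- Linear, both SDs 0.04: above 99% for every method.

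The gain from a last-visit contrast therefore depends on the inputs and can vanish or reverse in aim I. Over three variance splits and linear or immediate build-up, the baseline-adjusted average of later visits had power equal to or above the all-visit average, and a less diluted estimate.

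**The case against.** The strongest reply is that the article never says all weekly values are pooled with equal weight, or that the first visit counts as an outcome. It condenses a fuller document, where visit coding and the contrast may be settled. That stands in part: a pooled effect is the natural reading, not a stated one. But the article does state the outcome, model, contrast and covariates, and followed as written they leave the period baseline as an outcome.

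Two stronger readings are tempting. A reader might infer that including the first visit by itself halves the effect. It does not: that costs 1/6 or 1/3, and one half also requires linear build-up averaged over all visits. A reader might also infer that week 1 is known to be pre-training. Trial design {8} covers only the return visit after washout, and Table 1 files weeks 1 to 6 under follow-up, with a separate vHIT at enrollment. The pre-training status of week 1 is likely but not stated.

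Two further points have force. A mean difference over the training period is a legitimate target if chosen on purpose; the article does not say it was. And the week 13 or week 7 value is measured after randomization and may carry effects of the first intervention, so adjusting for it can distort the contrast if carryover exists.

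**Conclusion.** The point holds as a weakness that should be corrected, not as a flaw that invalidates the trial. The primary analysis fixes neither the time point nor the role of each period's first VOR gain value, and at least the value opening period 2 is in effect a pre-training baseline.

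The loss of 1/6 or 1/3 rests on equal visit weights and on both periods starting before training. The total dilution, about 0.37 to 0.83 of the end-of-training effect, rests on assumed time courses. A large power loss cannot be claimed in general, because the documents give neither a time course nor a within-participant variance split. Moving the pre-training value from outcome to covariate is the part of the remedy that depends least on these assumptions.

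**What to change.** - Use each period's pre-training VOR gain as a covariate and remove it from the outcomes: week 1 or the enrollment vHIT for period 1 (state which, and whether week 1 precedes training), and week 13 (aim I) or week 7 (aims II and III) for period 2.
- Name the primary contrast in advance. The preferred choice is the IVE-VPT difference at the last training visit (weeks 6 and 18; weeks 3 and 9), from a repeated-measures model with treatment-by-week terms. This matches the before-to-after change behind the sample size. Intermediate weeks stay in the model to support missing data and describe the time course. Keep these terms distinct from the carryover test, so that gradual build-up is not read as carryover.
- If an average over the period is intended, say so and average only the visits after the period baseline.
- Report the analysis without the period baseline as a sensitivity analysis, because the period 2 value may carry period 1 effects.

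The cost is analysis wording; every visit is already scheduled. The downside is that a last-visit contrast can be less precise than an average of post-baseline visits when the effect comes early or visit-to-visit noise is large.

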### Sample size {14}

We have based our estimate of sample size on data published in healthy adults (21–58 years old) using the IVE paradigm, whose age reflects our target patient population [30]. In that study, active VOR gain pre-adaptation was 0.92 ± 0.18 and active VOR gain post adaptation was 1.11 ± 0.22. Therefore, using the mean difference between pre- and post-adaptation of 0.19 with a standard deviation of 0.18, we would need a minimum of 9 participants to be able to reject the null hypothesis with a probability (power) of 0.8, presuming *α* < 0.05 (PS Power and Sample Size Calculations, version 3.1.2). Presuming a 25% attrition, we will recruit at least 12 participants for each of the IVE-VPT and VPT-IVE patient cohorts (aims). We aim to enrol 24 service members at the FBCH site and 24 civilians at the JHU Outpatient Center for each of aims I–III.

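### A non-significant interaction test is read as verifying equal carryover, but with about 18 participants per sequence it has only about 7% to 13% power for differential carryover of 0.05 to 0.10 in VOR gain

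*Protocol article*

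**What the plan says.** The protocol article's section on statistical methods {20a} fits a mixed model to weekly VOR gain, compares the interventions, and estimates period and carryover effects. It sets out an expectation: "With substantial washout periods for each aim, we do not expect there to be substantial differences in the carryover effects between intervention sequences". It then gives the check: "We will verify there are no differences in the carryover effects by testing for an interaction between treatment and time". If the test is significant, "we will focus our analysis on patient outcomes in the first period, and disregard outcomes in the following period". The level is 0.05, two-sided. No margin, precision target or return-to-baseline criterion accompanies the check.

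Washout lasts 6 weeks in Aim I and 3 weeks in Aims II and III (Intervention description {11a}). Table 1 lists a video head impulse test (vHIT) at enrolment, under "One-time VOR characterization". It then lists weekly vHIT in weeks 1–6 and 13–18 for Aim I, in weeks 1–3 and 7–9 for Aims II and III, and again at 6 months. Trial design {8} says how the measures from the first return visit after washout are used: they feed into the training that follows. Neither the enrolment vHIT nor the first post-washout vHIT is named as a check on washout.

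**The concern.** A failure to reject is evidence of no difference only if the test would probably have rejected had a relevant difference existed. In a two-sequence, two-period design the treatment-by-period interaction is a comparison between participants: each person's two-period total is compared across sequences, so between-person variation stays in. (The protocol writes treatment by time for the primary outcome and period by intervention for the secondary one. I read both as this contrast.)

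Carryover is not far-fetched here. The device is meant to raise VOR gain towards normal, and outcomes are re-measured at 6 months. If some of the training effect outlasts a 3- or 6-week washout, and differs between interventions, the trial would probably pass its own check. It would then report a treatment difference described as free of differential carryover when that had not been shown.

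**Working it through.** **The plan's own figure.** Sample size {14} plans on a pre–post change, "using the mean difference between pre- and post-adaptation of 0.19 with a standard deviation of 0.18", and states "we would need a minimum of 9 participants to be able to reject the null hypothesis with a probability (power) of 0.8". A paired t-test with n = 9 has power 79.2%, so 9 reproduces within rounding, and 9/0.75 = 12. This is a one-group pre–post calculation in healthy adults. The protocol states no IVE–VPT difference and no power for the carryover test.

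**Inputs.**
- Enrolment: 24 + 24 = 48 per aim, allocated 1:1, so 24 per sequence; 24 × 0.75 = 18 evaluable (from the protocol).
- SD s = 0.20, between the stated 0.18 and 0.22 (assumption).
- Correlation ρ = 0.6 (assumption). Reading 0.18 as the SD of the difference gives (0.18² + 0.22² − 0.18²)/(2 × 0.18 × 0.22) = 0.61.
- One value per period (simplification).
- Differential carryover λ = 0.05 or 0.10 (assumption): half or all of an assumed true difference of 0.10.

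**Precision of the interaction contrast.** SE = s√(2(1+ρ)) × √(2/n) = 0.20 × √3.2 × √(2/18) = 0.119. The 95% half-width is 2.03 × 0.119 = 0.24.

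**Power (two-sided 0.05).** About 7% at λ = 0.05 and 13% at λ = 0.10. Simulation with 20,000 runs and ρ = 0.61 gave 7.1% and 13.3%.

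**Sensitivity.**

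| Variant | λ = 0.05 | λ = 0.10 |
|---|---|---|
| SD 0.18–0.22, ρ 0.3–0.8, 18–24 per sequence | 6–9% | 11–22% |
| Six weekly values averaged per period (SD 0.18–0.20, ρ 0.5–0.8) | 7–10% | 13–25% |
| As the row above, plus enrolment gain as covariate | 10–20% | 27–61% |

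All are below 80%. For λ = 0.19 (a true difference as large as the planning effect, wholly retained), the unadjusted one-value test has 26–60%. Only with weekly averaging and covariate adjustment together can that extreme case pass 80%. For example, with SD 0.18, ρ = 0.61 and 18 per sequence, SE = 0.18 × √(2(1+5ρ)/6 + 2ρ − 4ρ²) × √(2/18) = 0.062, and power is 84%.

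**What retention does to the two-period estimate.** Let the period-1 effects be a (IVE) and b (VPT), with share c of each retained additively.
- Raw period values: ½[(a − (ca + b)) + ((cb + a) − b)] = (a − b)(1 − c/2). With a − b = 0.10 this is 0.075 at c = 0.5 and 0.050 at c = 1.
- Equal absolute retention k in both sequences: ½[(a − (k + b)) + ((k + a) − b)] = a − b. No bias.
- Change from each period's first, pre-training visit: the period-2 changes are (ca + b) − ca = b and (cb + a) − cb = a. The estimate is again a − b.

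**A more precise contrast on scheduled data.** Take the between-sequence difference in VOR gain at the first post-washout visit, adjusted for enrolment gain: SE = s√(1 − ρ²) × √(2/n) = 0.20 × 0.8 × 0.333 = 0.053, half-width about 0.11. The fair comparator is the interaction contrast with the same covariate: SE = s√(2(1+ρ) − 4ρ²) × √(2/n) = 0.20 × √1.76 × 0.333 = 0.088. The ratio is 1.7, and 1.6 to 1.7 over ρ from 0.4 to 0.8. The direct contrast has about 15% power at λ = 0.05 and 44% at λ = 0.10.

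**The case against.** **The post-washout data are already used.** A reader might infer that the vHIT values which bear on washout are ignored. They are not. The week-13 or week-7 value belongs to the weekly series in the primary model, and measures from that visit also shape period-2 training. Whether enrolment gain is a covariate is ordinary analysis-plan content. What stands is that neither value is named as evidence on washout.

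**The plan estimates as well as tests.** The model is said to estimate carryover effects, so an estimate may well be reported. That is fair, but the stated decision and the claim of verification still rest on the significance test.

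**Bias of 25–50% is not established.** A reader might infer that the trial will understate any device advantage by that much. The documents give no retained share and no IVE–VPT difference, and the article does not say how period baselines enter the model. The attenuation needs raw period values and proportional retention; under either alternative in the working it is zero.

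**The replacement is also weak.** This is correct for differential carryover: 15% and 44% are not adequate power. A reader might also take the direct contrast to be two or three times as precise, but with equal covariate adjustment the advantage is 1.6 to 1.7. It earns its place as an estimate with an interval, not as a second pass/fail test.

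**Change from enrolment is confounded.** Without an untreated group it mixes retained training effect with spontaneous recovery. In Aim II it also includes gait and balance exercise begun at washout. It cannot prove or disprove washout.

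**Conclusion.** The point holds for what the check is said to show. At this sample size a non-significant interaction does not verify that carryover is equal between sequences. Under the stated assumptions power is about 7% and 13% for differential carryover of 0.05 and 0.10. For differences up to 0.10 it stayed below 80% in every variant examined. An interval of about ±0.24 cannot exclude differential carryover as large as the 0.19 planning effect.

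The SD is taken from the protocol's stated range. The correlation, the true difference and the retained shares are assumptions. Any attenuation of the treatment estimate is a conditional possibility, not a finding. The conclusion does not depend on carryover being present, only on the test being unable to rule it out. The error rate of the rule that drops period 2 after a significant test is a separate matter.

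**What to change.** 1. Delete the statement that the interaction test verifies equal carryover.
2. In each aim, report the between-sequence difference in VOR gain at the first post-washout visit before period-2 training (week 13 in Aim I, week 7 in Aims II and III), adjusted for enrolment vHIT gain, with its 95% CI.
3. Interpret the two-period estimate beside that interval. State any attenuation (half the retained share) as conditional on raw period values and proportional retention.
4. Mean change from enrolment to that visit, by sequence, may be shown as description only, noting spontaneous recovery and, in Aim II, the gait and balance exercise started at washout.

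The cost is one ANCOVA per aim on data already scheduled, a change of wording, and a weaker stated reassurance about carryover. The direct contrast will still have low power for small differential carryover, and the report should say so.

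### The carryover gate, which drops period 2 when a test at 0.05 is significant, raises the primary test's type I error to about 0.064 to 0.084 and gives little protection against carryover

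*Protocol article*

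**What the plan says.** All of this stands in the Protocol article, Statistical methods for primary and secondary outcomes {20a}. A generalized linear mixed model compares VOR gain between interventions and estimates period and carryover effects. On carryover the plan says: "We will verify there are no differences in the carryover effects by testing for an interaction between treatment and time". The consequence follows directly: "If this interaction is statistically significant at *α =* 0.05", then "we will focus our analysis on patient outcomes in the first period, and disregard outcomes in the following period". The paragraph ends with: "All statistical tests will be conducted as two-sided for an *α* of 0.05". No adjustment is stated for choosing the analysis from the data.

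The next paragraph, on compensatory saccades, presents its analysis as similar to the primary one but words the test differently: "estimating carryover effects by testing for an interaction between period and intervention".

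**The concern.** This is the classical two-stage crossover procedure. In a two-period, two-sequence design, the test of differential carryover compares participants' sums over both periods between sequences, and the fallback compares period-1 values between the same two groups. The statistics are positively correlated because each contains the period-1 data. When the gate opens by chance, the analysis therefore moves to the comparison that is then most likely to be falsely significant. The 0.05 stated for the primary test no longer describes the procedure that will be run.

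The gate is also meant to verify that carryover does not differ. It is a between-participant test in a trial whose sample size comes from a within-participant calculation, so a non-significant result says little. Both points affect the primary efficacy claim in each of aims I to III.

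**Working it through.** **The plan's own figure.** Sample size {14} works "using the mean difference between pre- and post-adaptation of 0.19 with a standard deviation of 0.18" and concludes "we would need a minimum of 9 participants to be able to reject the null hypothesis with a probability (power) of 0.8". A paired calculation with noncentral t gives power 0.792 at n = 9 and 0.843 at n = 10, so 9 is reproduced within rounding. Allowing for 25% attrition, 9 / 0.75 = 12, as stated. This is a pre/post calculation and does not size a comparison between groups in period 1. If 0.18 is taken as a between-participant SD, a period-1 difference of 0.19 has power of about 0.56 with 9 per sequence and 0.70 with 12.

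**Inputs from the document.** Gate and treatment tests are at two-sided 0.05 ({20a}). Enrolment per aim is 24 + 24 = 48 ({14}), allocated 1:1 ({16a}), so 24 per sequence. After 25% attrition, 24 × 0.75 = 18 completers per sequence.

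**Assumptions.** The between-period correlation rho is not given, so I use 0 to 0.8. The SD of a period value is taken as 0.20, between the 0.18 and 0.22 quoted in {14}; it matters only when carryover or a treatment effect is present. Each participant contributes one value per period, and t-tests stand in for the mixed model.

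**Step 1: why the error rises.** The correlation between the carryover statistic and the period-1 statistic is sqrt((1 + rho)/2): 0.71 at rho 0, 0.81 at 0.3, 0.90 at 0.61 and 0.95 at 0.8. With equal variances in the two periods, sums and within-participant differences are independent, so with no treatment effect and no carryover:

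overall error = 0.95 × 0.05 + 0.05 × P(period 1 rejects, given that the gate fires).

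| rho | P(period 1 rejects, gate fired) | Formula | Simulated overall error |
|---|---|---|---|
| 0 | about 33% | 0.0475 + 0.0165 = 0.064 | 0.064 |
| 0.3 | about 44% | 0.0475 + 0.0220 = 0.070 | 0.068 |
| 0.61 | about 58% | 0.0475 + 0.0290 = 0.077 | 0.075 |
| 0.8 | about 70% | 0.0475 + 0.0350 = 0.083 | 0.084 |

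Formula and simulation agree within about 0.002. The ungated crossover test simulates at about 0.05 throughout. The ceiling, if period 1 always rejected once the gate fired, is 0.0475 + 0.05 = 0.0975. The result hardly depends on the number of participants. If the endpoint is change from each period's first week, the simulated error is lower, about 0.060 to 0.068 (weekly variance components assumed).

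**Step 2: can the gate detect carryover?** Take a differential carryover of 0.10. The standard error of the sequence difference in sums is 0.20 × sqrt(2(1 + rho)) × sqrt(2/18). At rho 0.61 this is 0.20 × 1.794 × 0.333 = 0.120, so the noncentrality is 0.10 / 0.120 = 0.84 and power is about 13%. Over rho 0.3 to 0.8, power runs from about 15% down to 12%.

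**Step 3: what the gate prevents.** With the same carryover of 0.10 and no treatment effect, the crossover estimate is biased by 0.10 / 2 = 0.05. False-positive rates for treatment are:

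| rho | With the gate | Crossover analysis always |
|---|---|---|
| 0.3 | 0.22 | 0.24 |
| 0.61 | 0.36 | 0.38 |
| 0.8 | 0.59 | 0.64 |

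The gate removes very little of the error that it exists to prevent.

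**Step 4: the fallback's power.** For a constant treatment difference of 0.10, the period-1 noncentrality is 0.10 / (0.20 × 0.333) = 1.5, giving power of about 31%. The crossover test at rho 0.61 has a standard error of 0.5 × 0.20 × sqrt(2 × 0.39) × 0.333 = 0.0294, a noncentrality of 3.4 and power of about 91%.

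**The case against.** **The inflation is modest and the rule is disclosed in advance.** True: it is roughly 1.5 to 3.5 percentage points, and less with a change-from-first-week endpoint. But it exceeds the stated 0.05 at every correlation examined, and the plan obtains nothing useful in exchange.

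**The remedy holds 0.05 only when carryover does not differ.** This stands. With a carryover of 0.10, the ungated analysis has a false-positive rate of about 0.24 to 0.64, slightly worse than 0.22 to 0.59 under the gate. Only a period-1 primary analysis holds 0.05 in both situations, at a heavy cost in power. The choice is a trade-off. It does not rescue a gate that leaves nearly all of the bias in place.

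**A stronger reading is tempting.** Because the outcome is "VOR gain, which is measured weekly for each subject in each intervention period", a reader might take the interaction with time as treatment by week and infer that period 2 would be discarded precisely when the treatment works. The documents do not support that reading. The test is tied to carryover between sequences, the consequence is framed by period, and the parallel secondary analysis names period and intervention. Rates for how often such a test would fire need weekly variance components that the protocol does not give, and type I error would stay near 0.05 under that reading. What remains is a loose word worth correcting.

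**The correlation might be thought known.** A value of 0.61 follows from {14} only if 0.18 is the SD of the pre/post difference. It is also the quoted pre-adaptation SD, and the data come from healthy adults in a different setting. It serves here only as one assumed point.

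**Conclusion.** The concern holds for the treatment-by-period gate. As written, the primary procedure has a type I error of about 0.064 to 0.084 (rho 0 to 0.8, 18 completers per sequence, no carryover), against the stated 0.05. When the gate fires by chance, the period-1 test is falsely significant in about 33% to 70% of trials. A non-significant gate cannot establish that carryover is absent, since it would miss a differential carryover of 0.10 in about 85% to 88% of trials (SD 0.20, rho 0.3 to 0.8). The exact size depends on rho and on the endpoint's form, neither of which can be settled from the article; the direction does not change over the ranges examined. The wording about time is a secondary point of clarity and not a separate fault in the error rate.

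**What to change.** In {20a}:

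- Delete the significance gate. Fix the two-period model (treatment, period, site, participant) as the primary analysis whatever any carryover test shows.
- Report the carryover (sequence) estimate with its 95% confidence interval as description, without a decision attached.
- Always report the period-1-only comparison as a prespecified sensitivity analysis.
- Show washout directly by comparing, by sequence, VOR gain at the first period-2 visit (week 13 in aim I, week 7 in aims II and III) with week 1. Table 1 already schedules vHIT at these visits.
- Name the interaction as treatment by period in the primary paragraph, to match the secondary one, so that it cannot be programmed as treatment by week.

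The cost is analysis wording only; no visits, participants or data collection change. The price in inference should be stated openly. If differential carryover exists, the primary estimate is biased by half of it and false positives rise well above 0.05. The period-1 sensitivity analysis is free of that bias but has only about 31% power for a 0.10 difference, so a disagreement may be hard to see and a non-significant period-1 result should not be read as contradiction.
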